## Outcomes

### The modeling phase (phase 1 study)

Both qualitative and quantitative data will be collected from both staff groups through semi-structured face-to-face interviews and focus groups. A set of questions to stimulate responses from the staff members will be generated according to Patton’s [28] recommendations and included in an interview protocol. The interviews will be used to explore nursing staff’s past experience and role in implementing an intervention focused on QoL measurement, whereas focus groups with nursing staff members will enable them to explore their perspective about a draft version of the INFO-QoL they will receive a week before the scheduled focus groups sessions. Two researchers with experience in palliative care will lead the interviews.

In both units, staff members’ knowledge on QoL will be assessed through a web survey using the INFO-QoL questionnaire before randomizing the site that will receive the intervention and after implementing the intervention.

Demographic information will be collected, including age, gender, level of education, professional role, years in their professional role, and years in PC.

### The exploratory trial (phase 2 study)

#### Feasibility of intervention

Feasibility will be measured in terms of time taken to organize and perform the intervention and to train professionals on QoL.

Also, fidelity of intervention will be assessed relating to deviations from the procedures and uncompleted measurements (with reasons), recorded using structured staff self-report checklists.

In addition, professionals will be asked to rate their competence and level of confidence in delivering the intervention at different points in time.

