a. Component 1: ensure that treatment plans and evaluations focus on patient rather than disease i. Goal: to educate staff about QoL issues and about interventions that promote a better QoL ii. Activities: discuss the following topics: – What is QoL in palliative care patients? – What are the dimensions that contribute to a person’s QoL? – What are the determinants of changes in self-assessment of QoL? – How staff should propose, use, and score QoL tools to patients – How palliative care staff can effect changes in patients to improve their QoL b. Component 2: the Palliative Outcome Scale (POS) as an integral component of the intervention i. Goal: patient and family education on using outcome measures ii. Activities: present the purpose of QoL assessment to patients and their families; educate patients on using the POS c. Component 3: QoL measurement using the POS i. Goal: to promote cohesive, coordinated patient- and family-centered care ii. Activities: screening (i.e., baseline) and monitoring individual patients (morning shift), record individual and overall scores on individual INFO-QoL form, and discuss results to inform clinical decision during unit staff briefing
4. Mode of delivery
a. Component 1: small group education session (6–8 palliative care nurses) i. Use combination of written and verbal presentation and group discussion ii. Written presentation: case-based materials, self-study binders, poster iii. Verbal presentation: evidence on QOL issue in palliative care iv. Group discussion: elicit case discussions to focus on issues related to patients’ QoL b. Component 2: nurses-patient and family face-to-face interaction i. Use combination of written material and verbal communication ii. Written materials, such as handout on QoL issues, and poster with large print and simple language hanging in the inpatient hospice unit iii. Verbal communication using a slow rate of speech, simple and common words, short sentences, and a teach-back technique c. Component 3: individual QoL measurement i. Nurse team leader is responsible to manage the measurement (i.e., schedule the measurement, prepare documentation, assign patient to nurse or nursing assistant, oversee completion of QoL measurement) ii. Nurse or nursing assistant who perform the QoL measurement motivates patient to improve compliance iii. Staff discusses results and gives feedback of results and care plan to patient
5. Dose

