a. Component 1: self-study binders given 2 weeks before the education bundle program session; one small group education session of 3-h duration (repeated at different time points to allow all staff to participate) b. Component 2: education session of about 10/15-min duration c. Component 3: measurement within day 3 from admittance, days 8–10, day 15 and then once a week; patient feedback at the same day of the measurement

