### The exploratory trial (assessing feasibility and piloting method)

As the INFO-QoL is being implemented throughout the unit and it will be difficult to deliver the intervention randomly to some patients but not to others, the feasibility stage will have a quasi-experimental non-equivalent comparison group before/after design. Although randomized controlled trials represent the gold standard, and quasi-experimental designs have a weakened confidence in making causal assertions that the results occurred because of the intervention, quasi-experimental designs can also provide useful information to establish whether (and to what extent) an intervention is effective. A non-equivalent comparison group design is the strongest of the quasi-experimental designs and can provide good evidence for nursing practice. Quasi-experimental designs are more feasible and more commonly conducted for nursing studies in clinical settings. This design will enable the researcher to pilot the components and methods and the feasibility of the INFO-QoL, in order to assess its acceptability in practice and determine whether the INFO-QoL is delivered according to the study protocol. It will also offer the opportunity to determine potential effectiveness of the INFO-QoL in improving patient QoL.

To partially address selection bias, the INFO-QoL described in Table 2 will be introduced randomly into unit 1 (intervention unit), while patients and staff in unit 2 (comparison unit) will continue with traditional clinical practice. By gathering pre-test data, we can compare the equivalence of the two groups on antecedent variables before introducing of the independent variable [25]. The study will inform methods for the future phase 3 trial in determining sample size and the power of the trial, recruitment, follow-up, and suitability of measures. For the purpose of this study, the type and quality of care delivered by sites will not be assessed: it will be assumed to be at least comparable between the two hospice units.

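### POS completion is counted from the delivering unit's own checklists, with no stated cross-check against the INFO-QoL forms or POS data, so it may be overstated

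*Protocol article*

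**What the plan says.** The section Feasibility of intervention names one data source for fidelity: "fidelity of intervention will be assessed relating to deviations from the procedures and uncompleted measurements (with reasons), recorded using structured staff self-report checklists". It mentions no observer, audit or comparison with records. The section on the exploratory trial makes fidelity a purpose of the design, which is meant to "determine whether the INFO-QoL is delivered according to the study protocol".

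Table 2 shows who delivers the measurement component. The bedside task falls to unit staff ("Nurse or nursing assistant who perform the QoL measurement motivates patient to improve compliance"), and the nurse team leader is to "oversee completion of QoL measurement". It also shows what is written down and when. Staff are to "record individual and overall scores on individual INFO-QoL form, and discuss results to inform clinical decision during unit staff briefing", and the dose is "measurement within day 3 from admittance, days 8–10, day 15 and then once a week", with "patient feedback at the same day of the measurement".

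The section Potential effectiveness collects the POS as an outcome at T0, T1 and T2, on the same days as the first three measurements in Table 2. It assigns a blinded research assistant to the comparison unit and names no separate assessor for the intervention unit.

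**The concern.** A checklist of omissions depends on somebody noticing an omission and writing it down. A measurement that was simply forgotten is easy to leave off. A count built from the schedule works the other way: a due measurement with no form is missed by default, whether or not anyone recorded it.

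The first research question, under Operational definitions, asks whether the procedures were carried out as intended, and feasibility is part of the primary objective. The results are to inform a phase 3 trial. If the completion rate is too favourable, a measurement schedule that the unit could not keep may go forward unchanged, and a null POS result becomes harder to interpret.

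**Working it through.** The article states no fidelity figure, threshold or expected rate, so there is nothing to reproduce. The check has three parts.

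**1. What each source can show**

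| Fidelity element | Staff checklist | INFO-QoL form / T0–T2 POS data |
|---|---|---|
| POS done or not | yes, if listed | yes: scores present or absent |
| POS done inside its window | yes, if listed | only if the form is dated, which the article does not state |
| Reason for an omission | yes | no |
| Patient and family education | yes, if listed | no |
| Discussion at the briefing | yes, if listed | no |
| Same-day feedback | yes, if listed | no |

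The forms can therefore improve the first row, and the second if a date is present. They cannot replace the checklist for the rest.

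**2. Number of measurements open to checking**

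Inputs from Sample size: 17 patients per unit and period, or 23 after the attrition allowance. Input from Table 2 and Potential effectiveness: three fixed time points.

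- 17 × 3 = 51
- 23 × 3 = 69

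This is an order of magnitude for T0 to T2. Deaths and discharges reduce it, and the weekly measurements after day 15 add to it, so 69 is not a ceiling. With 51 to 69 due measurements, each unlisted omission raises the reported rate by 1/69 = 1.4 to 1/51 = 2.0 percentage points.

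**3. Possible size of the overstatement**

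Let *c* be true completion and *u* the share of missed measurements that the checklist does not list. Then

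reported completion = *c* + (1 − *c*) × *u*

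Neither *c* nor *u* is in the article. Both are assumptions.

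| True completion *c* | *u* = 0 | *u* = 10% | *u* = 25% | *u* = 50% |
|---|---|---|---|---|
| 60% | 60% | 64% | 70% | 80% |
| 70% | 70% | 73% | 77.5% | 85% |
| 80% | 80% | 82% | 85% | 90% |
| 90% | 90% | 91% | 92.5% | 95% |

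Worked example: with *c* = 70% and *u* = 50%, 0.70 + 0.30 × 0.50 = 0.85. For *u* from 10% to 50% the overstatement ranges from 1 point (90% reported as 91%) to 20 points (60% reported as 80%). It is zero when every omission is listed.

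**The case against.** The case for leaving the plan alone has real weight.

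- **The form is not an independent record.** A reader might infer that it is an objective, dated trail. The article supports neither word. Staff of the same unit complete the form, and it is stated to hold scores only. This stands. The form still has an advantage for the one item at issue, because completion requires actual scores and an absent form counts as missed without anyone having to report it.
- **Omissions may surface anyway.** A missed POS at T0 to T2 in the intervention unit would probably appear as a missing outcome value, and the team leader has oversight of completion. So a missed measurement need not stay hidden unless the person responsible writes it down. This also stands, but the article does not carry that information into the fidelity measure, which remains the checklist.
- **Other process data exist.** Management actions are taken from charts and ad hoc documentation, and there are patient questionnaires, staff interviews, time records and competence ratings. A reader might infer that the study could not tell an ineffective intervention from one that was not delivered. That goes too far, since these sources give partial evidence on delivery. None of them is stated to count completed POS measurements.
- **This is a condensed article.** Reconciliation of checklists with forms may be described in the full protocol, which is not shown. The point is therefore limited to what the article fixes: a named source for uncompleted measurements that is weaker than data the study already generates.

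**Conclusion.** The point holds in a limited form. Staff self-report is the only fidelity source that the article names, the reporters belong to the delivering unit, and no cross-check of POS completion against the forms or the T0–T2 data is stated. The completion rate may be overstated. A reader might go further and conclude that it is biased upward, but the article has no data on under-reporting. The checklists are also structured and ask for reasons, which may keep omissions from going unlisted.

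The range of 1 to 20 points rests entirely on the assumed values of *c* and *u* and shows sensitivity only. Fidelity is one feasibility measure among several, and no stated figure or analysis is invalidated. This is a cheap improvement to how one result is counted.

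**What to change.** For each consented patient in the intervention unit, derive the due POS measurements from the admission date and the Table 2 schedule. A measurement is due only if the patient is alive and in the unit. Report:

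1. the proportion of due measurements with a completed POS form;
2. the proportion completed inside the scheduled window, adding a date to the form if it has none.

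Keep the staff checklist for the reasons behind omissions and for what a score form cannot show: patient and family education, discussion at the briefing, and same-day feedback. Label those results as self-reported. A box for feedback or briefing ticked by the same staff would also be self-report and would not verify them.

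The cost is a sentence or two in the protocol, possibly one date field, and abstraction of roughly 51 to 69 forms for T0 to T2, plus any weekly forms after day 15. The fidelity figure may come out less favourable than the checklist would give.

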#### Feasibility of the study

Study feasibility will be assessed in terms of time taken to obtain patients’ informed consent and recruitment and patient dropout rates.

#### Acceptability of the study

Acceptability will be evaluated in terms of proportion of eligible patients (who were approached about the study) accepting to participate in this study.

##### Acceptability of intervention from patients’ perspective

Once the delivery of the intervention is completed, acceptability will be examined using a semi-structured questionnaire designed and developed for this study. Patients will be asked to appraise the intervention in terms of appropriateness and usefulness in identifying their needs using a QoL tool and to suggest ways to enhance its acceptability and to identify any missing elements [29].

##### Acceptability of intervention from staff’s perspective

Acceptability will be assessed using a semi-structured interview including five open questions.

After implementing the intervention—at the end of a 3-month period—staff members’ acceptability will be explored in terms of relevance, appropriateness, and usefulness in addressing QoL of palliative care patients.

To enhance the completeness and acceptability of the intervention, staff members will be asked to suggest ways to modify any aspects of the intervention and their professional views use the INFO-QoL as a standard practice in the unit.

Prior to staff interviews, the intervention (INFO-QoL) will be provided to staff in the intervention unit, giving a fundamental overview of QoL as the main focus of palliative care. Staff in the intervention unit will then be asked:How would you comment on the relevance of the intervention in addressing palliative care patients’ QoL?How would you appraise the intervention overall in terms of its appropriateness in addressing palliative care patients’ QoL?How would you appraise the intervention overall in terms of its usefulness in addressing palliative care patients’ QoL?Would you suggest modifying any components and/or activities of the intervention?Would you recommend using the INFO-QoL as a standard practice within the unit?

#### Potential effectiveness

QoL will be assessed by collecting data before (period I: 3 months) and after (period II: 3 months) the intervention and comparing QoL scores in the intervention and comparison unit using the Italian version of the Palliative Outcome Scale (POS). The QoL assessment will be performed within day 3 (T0) from admittance, on day 8–10 (T1), and then on day 15 (T2). To reduce detection bias, a trained research assistant—who will be blind to intervention or comparison status of the unit—will administer the POS to patients in the comparison unit. Staff will receive full disclosure of the study purpose. This outcome measure has been originally validated in advanced cancer patients in the UK. Cronbach’s alpha for internal consistency was 0.65 and kappa for reliability ranged from 0.8 to 0.62. The POS includes ten items on physical, psychological, and spiritual dimensions. Responses to each of the ten questions range on a scale from 0 to 4. A score of 0 indicates “not a problem at all” and 4 indicates “overwhelming” for the patient. The completion time is 7 min [30]. The psychometric properties of the Italian version of the POS were acceptable, Cronbach’s alpha coefficient was 0.65, and intra-class correlation coefficient was 0.72 [31].

Demographic patient information will be collected, including age, gender, education level, marital status, primary cancer site, and length of time since diagnosis. We assume that if patients are admitted to hospice with a primary diagnosis of cancer, they will all have advanced stage cancer.

#### Patient management

Patient management will be evaluated using an adapted version of the composite patient management score by Detmar et al. [32]. All QoL-related management actions taken by staff for patients will be calculated by summarizing all the actions taken. Data will be collected from medical and nursing charts and ad hoc documentation, which will comprise the terminology included in the QoL tool (i.e., the POS) to collect actions delivered to patients for each of impaired QoL dimensions resulting from the POS score. Data on these actions will be elements of care pathways including but not limited to medications, interventions, nutrition and dietary, vital signs, diagnostic tests, referrals and consultations, patient and family counseling, and education.

## Ethics statement

The INFO-QoL research project was approved by the IRCCS AOU San Martino—IST Regional Ethics Committee (Study #335REG2014). All participants—both healthcare professionals and patients—will be asked to sign an informed consent form. Preliminarily, they will receive a one-page study information sheet, which will be discussed, and then they will be asked if they would be willing to participate in the study. Patients will also be informed that refusing to participate do not affect the care they need and that they could withdraw their consent at any time. Also, participants will be informed that their data will be protected from inappropriate disclosures according to Italian laws and regulations. Healthcare professionals invited to participate will be advised that declining does not lead to any penalty or loss of benefits otherwise entitled.

## Discussion

Despite numerous publications on the issue of patient QoL, there is a paucity of evidence on how best to address QoL assessment in clinical practice. The findings of our project could add important evidence-based knowledge on this topic. Therefore, our results can help build knowledge about what components to include in modeling an intervention focused on QoL assessment, which is useful for other implementation projects to learn from. A clinical intervention focused on QoL assessment provides innovation for oncology and palliative nursing in several ways: (1) fostering the simultaneous care model; (2) ensuring that the voices (needs) of people with advanced cancer are heard; (3) helping at screening and monitoring patients’ needs to fully personalize care through evidence-based nursing interventions; (4) supporting the evidence-based practice movement to ensure quality of service, effectiveness and accountability, and personalized care; (5) facilitating identification of what works and what does not work in delivering clinical nursing interventions aimed both at measuring and improving patients’ QoL; and (6) assuring that patients’ wishes and preferences will be recorded and understood by health professionals delivering care to them.

Early initiation of palliative care has been proved to improve QoL significantly in the outpatient setting [33]. Although this study will be focused on hospice inpatient units, it will potentially also contribute to gain an in-depth insight into developing and implementing complex interventions focused on QoL assessment in settings other than hospice units, such as hospital and community settings [29, 34]. It may contribute to improving patient’s QoL in advanced disease trajectory as well. A systematic literature review showed that QoL assessment leads to improved delivery of patients’ physical, psychological, and social needs [2] and that more rigorous studies are necessary to establish a routine clinical practice approach for identifying and addressing patients’ unmet needs. The innovative approach identified and piloted in our study may help to fulfill this need, as we have rigorously applied the MRC framework to palliative care patients in clinical practice, in order to address these key issues identified in the literature.

This study may also contribute towards the development of research in palliative care practice, addressing a relevant topic for patients, families, and healthcare professionals. The strength of the study is related to the multiple components of the intervention based on data currently available. The structured approach of the intervention may provide a method for identifying informed care plans and improving patients’ outcomes. Healthcare palliative professionals involved may find the intervention acceptable for delivery in clinical practice after receiving formal training in all the preliminary phases of the study. Moreover, as a consequence of the staff’s commitment, training/education received, and expectation of improved patient outcomes, they may decide to maintain use of the INFO-QoL intervention as standard practice beyond the duration of this study.

## Abbreviations

CVI: Content Validity Index
EONS: European Oncology Nursing Society
I-CVI: Item level Content Validity Index
INFO-QoL: INtervention FOcused on QoL measurement
MRC: Medical Research Council
PC: Palliative care
POS: Palliative Outcome Scale
PROMs: Patient-Reported Outcome Measures
QoL: Quality of Life
S-CVI: Scale level Content Validity Index
WHO: World Health Organization
